## Abstract

**Background:**

People living with diabetes must manage a range of factors for optimal control of glycaemia and to minimise the risk of diabetes-related complications. Diabetes practitioners are expected to follow guidelines for the key process of care and clinical outcomes, to help people living with diabetes achieve clinical targets. In Australia, the performance of diabetes centres against guidelines is evaluated by the Australian National Diabetes Audit, an annual clinical audit and feedback activity. Previous work has identified areas for improvement in the feedback provided to participating diabetes centres and suggested additional educational and support resources to assist in using audit feedback for the development of quality improvement activities. This cluster randomised trial will test the acceptability, utility and impact on selected clinical outcomes of the developed study intervention (audit feedback and a tailored educational and peer support cointervention).

**Methods:**

Two-armed cluster randomised trial with Australian Diabetes Centres that participated in the Australian National Diabetes Audit in 2021 as the clusters, stratified by location and type of centre. We aim to recruit 35 diabetes centres in each arm. Both the intervention and control arms will receive an augmented feedback report, accompanied by a partially pre-populated slide deck. In addition, the intervention arm will receive a tailored theory-based intervention designed to address identified, modifiable barriers to utilising and implementing the recommendations from diabetes audit feedback. The co-primary outcomes are (1) HbA1c at the patient level, measured at 6 months after delivery of the intervention, and (2) the acceptability and utility of the augmented feedback and cointerventions at the practitioner level, measured at 3 months after delivery of the intervention.

**Discussion:**

This trial aims to test the effects of systematic development and implementation of theory and evidence-informed changes to the audit feedback delivered to diabetes centres participating in an established national clinical diabetes audit. Potential benefits of improved audit feedback include more optimal engagement with the feedback by end clinical users which, ultimately, may lead to improvements in care for people living with diabetes.

**Trial registration:**

Australian and New Zealand Clinical Trials Registry ACTRN12621000765820. Prospectively registered on June 21, 2021

**Supplementary Information:**

The online version contains supplementary material available at 10.1186/s13063-022-06910-9.

## Administrative information

Note: the numbers in curly brackets in this protocol refer to SPIRIT checklist item numbers. The order of the items has been modified to group similar items (see http://www.equator-network.org/reporting-guidelines/spirit-2013-statement-defining-standard-protocol-items-for-clinical-trials/).

## Introduction

### Background and rationale {6a}

Diabetes is a common risk factor for cardiovascular disease, stroke, amputation and microvascular complications including retinopathy, neuropathy and nephropathy [1]. It is estimated that 68% of people over 65 years of age with diabetes will die from cardiovascular disease and 16% from stroke [1]. Optimal diabetes management requires people with diabetes to simultaneously control multiple factors including blood glucose, blood pressure, lipids and lifestyle factors such as diet and physical activity. Optimal control of these underlying risk factors is strongly associated with better outcomes and reduced cardiovascular disease, stroke and microvascular complications in people living with diabetes [1–5]. While people living with diabetes often self-manage many of the contributing factors, there is a high need for healthcare involvement to manage medications and monitor clinical markers; hence, the utilisation of healthcare services is higher among people with diabetes than in the general population [6]. Additionally, many people living with diabetes struggle to follow all recommended care processes, although following these processes is associated with lower rates of both inpatient and outpatient hospital presentations and improved microvascular and macrovascular outcomes [4, 5, 7, 8]. Interventions to support optimal management of risk factors in diabetes, both by people with diabetes and the healthcare services they access, therefore have the potential to improve health outcomes and reduce hospital presentations.

The Australian National Diabetes Audit (ANDA) is a longstanding clinical audit and feedback activity which has been administered by Monash University and the National Association of Diabetes Centres (NADC) since 2013. This clinical audit routinely collects de-identified information about clinical markers (e.g. HbA1c, blood pressure and lipid levels) and process of care measures (e.g. proportion of patients receiving annual retinal examination) among people living with diabetes in Australia who attend health services based in primary care, secondary or community care and tertiary referral centres. During a 4-week period in May through to July of each year, data is collected for all consecutive patients attending participating diabetes centres, using a standardised data collection form (Additional file 1). Data is collated and analysed, and participating centres then receive feedback in the form of an individualised benchmarking report which is made available to centres in an electronic format. Currently, the individualised report is approximately 200 pages long and provides detailed information on clinical performance in terms of clinical and process measures. Each measure is benchmarked to the mean achieved across all participating centres. Clinical performance indicators are presented in the form of tables and bar charts, allowing individual centres to interpret their data and undertake quality improvement activities as they see appropriate. While these individualised reports are only released to the individual diabetes centre, the de-identified data across all centres is also collated into a national report that is publicly available [9].

Audit and feedback activities such as ANDA are commonly employed in health care to inform quality improvement activities, based on the assumption that healthcare practitioners and services are motivated to engage in best practice but may not be aware of suboptimal performance [10]. In a 2012 Cochrane review of the effects of audit and feedback on professional practice and healthcare outcomes (140 studies), audit and feedback was reported to generate small but meaningful improvements in practice and patient health outcomes across a number of different conditions and settings [10]. For compliance with desired practice (dichotomous outcomes), there was a median 4.3% absolute increase in desired practice (IQR 0.5 to 16.0%). For compliance with desired practice (continuous outcomes), there was a median 1.3% absolute increase in desired practice (IQR 1.3 to 28.9%). For patient outcomes (continuous), the median percent change was 17% (IQR 1.5 to 17%) [10]. While these changes may seem small, at a population level, they represent a substantial healthcare gain. The review recommended future studies of audit and feedback compare different approaches to its delivery.

Benefits of a large-scale audit such as ANDA include the ability to show variation in practice and highlight areas where there may be a lack of concordance between evidence-based recommendations and actual care, resulting in suboptimal outcomes [11]. Previous analysis of the ANDA data has shown variation in practice and outcomes and evidence-practice gaps in the form of prescribing and treatment gaps for lipid-lowering medication and antihypertensives for people with type 2 diabetes [12]. In addition, ANDA has documented a high prevalence of various cardiovascular risk factors for people with type 1 diabetes participating in ANDA [13], along with suboptimal HbA1c for people with type 2 diabetes [12]. Descriptive data from pooled ANDA reports show suboptimal mean HbA1c, blood pressure and lipid levels, with little change over time [9, 14, 15]. This lack of change in key clinical measures including HbA1c over multiple cycles of ANDA audit and feedback suggests that the current form of feedback may not be fully translating into reduced practice variation and optimal health outcomes.

Given that clinical and process of care outcomes for many centres indicate room for improvement with little change over time resulting from ANDA, there is a need to explore alternative, potentially more effective methods of audit feedback delivery that meet the needs of diabetes centres and stimulate quality improvement (QI) activities in areas where practice is suboptimal. Our previous qualitative study [16] used an approach based on the Consolidated Framework for Implementation Research (CFIR) [17] and sought to identify (i) how diabetes centres use the current ANDA feedback to inform QI activities, (ii) the barriers and enablers to optimal use of diabetes audit feedback in these centres, (iii) the data needs of the stakeholders, (iv) what format might be more beneficial for stakeholders to interpret and act on the feedback provided and (v) whether there are other feedback or practice improvement interventions that may assist.

The main desired changes to feedback we identified were a shorter report and a more engaging, simplified data visualisation style. Barriers to the use of feedback included access and knowledge about how to use the data provided to inform the development of QI activities. Perceived enablers of implementation included leadership engagement, peer mentoring and support to share experiences of using ANDA data to inform QI activities, and external policy and incentives to encourage participation, such as recognition of ANDA participation by professional and accreditation bodies. Potential cointerventions to augment the feedback and support QI development included exemplars from clinical change champions and peer leaders and educational resources to help facilitate change [16]. These results support our contention that the existing ANDA audit feedback may not be used optimally and inform the redesign of ANDA feedback and the development of educational and community of practice resources based on the needs of diabetes centres, underpinned by the CFIR and contemporary audit and feedback literature.

### Objectives {7}

#### Hypothesis

The systematic, theoretically underpinned, development and delivery of a tailored intervention of enhanced audit feedback and an educational and community of practice cointervention for diabetes healthcare professionals will improve the acceptability and utility of ANDA audit feedback and will subsequently improve healthcare professional practice and patient outcomes when compared to receiving audit feedback alone.

#### Objectives

This cluster randomised trial will test the acceptability, utility and impact on selected clinical outcomes of the developed study intervention (audit feedback and a tailored educational and community of practice cointervention). The specific objectives of this project are:To determine whether the implementation of redesigned ANDA feedback with or without the addition of tailored educational and community of practice resources leads to an improvement in HbA1c at 6 months and selected other clinical outcomes, when compared to previous auditsTo determine whether the redesigned ANDA feedback and tailored educational and community of practice resources are associated with improved practitioner perceptions regarding the acceptability and utility of ANDA feedback

### Trial design {8}

As the trial interventions will target participants who receive and act on ANDA feedback (health service staff and practitioners), effectiveness is best evaluated through a cluster randomised trial with clustering at a centre level. The framework of this trial is a superiority trial with 1:1 allocation.

## Methods: participants, interventions and outcomes

### Study setting {9}

The setting for this trial is Australian diabetes centres participating in ANDA.

### Eligibility criteria {10}

#### Inclusion criteria

##### Diabetes centres

Australian diabetes centres (Centres of Excellence, primary, secondary and tertiary care services) registered with the National Association of Diabetes Centres (NADC) will be eligible for inclusion in the trial if the following criteria are met: (i) at least one representative of the practice (the designated contact person for ANDA) provides written informed consent; (ii) the practice participates in ANDA in 2021 (irrespective of whether they have or have not participated in previous years). Differences between types of eligible diabetes centres are shown in Table 1.

**Table 1 Tab1:** Differences between types of eligible diabetes centres (based on the criteria set out by the NADC)

Type of centre	Definition
Primary care centres	General practices or community health centres that work closely with the local general practitioners to provide care for people with diabetes
Secondary care centres	Services with a range of full and/or part-time diabetes staff but who often do not have an endocrinologist as part of their usual team
Tertiary care centres	Diabetes centres that have the full range of diabetes service providers including endocrinologists, diabetes nurse educators, psychologists, dietitians and podiatrists on staff (full time) and have been accredited by the NADC
Centres of Excellence	Recognised diabetes centres that have demonstrated excellence in education, research, service delivery, practice/policy development and education. These centres must be tertiary-level facilities

##### Patient data

The study will not recruit patient participants. Rather, patient data for pre-determined fields relating to type 1 or type 2 diabetes mellitus care among people aged 18 years and over will be extracted from existing routinely collected and de-identified (coded) data reported as part of the ANDA annual audit.

#### Exclusion criteria

We are not collecting any additional data directly from patients, and we will not utilise ANDA data relating to people with gestational diabetes mellitus (GDM) or diabetes of unknown type. There are no additional exclusion criteria related to diabetes centres or to patient data.

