##### HbA1c at 6 months

HbA1c is routinely collected for patients from participating diabetes centres as part of ANDA. Baseline de-identified (coded) mean HbA1c percentage will be extracted for each participating diabetes centre from routine ANDA data collection in 2021. Follow-up data will be collected as part of the ANDA 2022 audit (6 months after delivery of the 2021 ANDA site reports).

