## Assignment of interventions: blinding

### Who will be blinded {17a}

The project lead and primary investigator will not be blinded to group allocation as they will be delivering the interventions, but they will only be aware of the site practice and outcome data pertaining to any given diabetes centre in a coded manner, as each participating diabetes centre has a unique identifying code. The ANDA Secretariat is the only person who has access to the codes linking diabetes centre IDs with their contact details and is not involved in the delivery of the intervention, assessment of outcome or analysis.

Other investigators and the biostatistician supervising the analysis will be blinded to group allocation. The data analysis team will be blinded to allocation details for the purpose of data analysis.

Participating diabetes centres will be blind to group allocation until the delivery of the interventions. Due to the nature of the intervention and control in this study, it will not be possible to blind the participating sites to the intervention they receive.

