## Statistical methods

### Statistical methods for primary and secondary outcomes {20a}

#### Primary outcomes

Differences between the experimental and control groups will be analysed by the intention-to-treat approach. For the first co-primary outcome of difference in HbA1c, we will use the linear mixed effects model to compare the between-group difference in mean HbA1c at 6 months after delivery of the intervention while adjusting for clustering of patients with site by including a centre random intercept. Appropriate transformations of the data will be undertaken in the event of departure from normality. Only if the first co-primary outcome is statistically significant at a two-sided level of significance of <0.05, we will test the second co-primary of acceptability and utility of interventions for superiority using the chi-squared or Fisher’s exact test as appropriate. This will preserve the overall type 1 error at <0.05.

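### The HbA1c comparison rests on whoever attends the 2022 audit, with only a centre intercept named in the model; pre-specify diabetes type and age as covariates and report attenders by arm

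*Protocol article*

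**What the plan says.** The background section (6a) describes the audit that supplies the outcome. "During a 4-week period in May through to July of each year", "data is collected for all consecutive patients attending participating diabetes centres". Under the eligibility criteria, no patients are recruited. The trial extracts "patient data for pre-determined fields relating to type 1 or type 2 diabetes mellitus care among people aged 18 years and over". Gestational diabetes and diabetes of unknown type are left out, and then: "There are no additional exclusion criteria related to diabetes centres or to patient data".

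Follow-up HbA1c comes from the 2022 audit, timed at six months from delivery of the 2021 site reports to the centres. The opening paragraph on primary outcomes describes the measure as the HbA1c of people attending participating centres for care.

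On blinding (17a), centres do not know their arm until the interventions are delivered, and from then on "it will not be possible to blind the participating sites to the intervention they receive".

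Statistical methods (20a) specify a linear mixed effects model for HbA1c, "adjusting for clustering of patients with site by including a centre random intercept". No patient-level covariate is named. Under secondary outcomes, the protocol says that the investigator group has no access to individual patient data for the audit's clinical measures and will extract means.

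**The concern.** This is a repeated cross-section. Those measured in 2022 need not be those measured in 2021, and who is measured is settled after randomisation, at centres that by then know their arm. The analysis pools two types of diabetes and all adult ages.

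Randomising centres makes the arms comparable in expectation at the time of randomisation. It does not guarantee that the mix of attenders stays comparable afterwards. Two routes matter:

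- **Chance.** Centres differ in the patients they see. The between-centre variance in the model reflects this in the standard error, but an imbalance that is actually observed stays in the estimate unless it is adjusted for.
- **QI activity.** The package is meant to prompt QI. If that work changed who attends in one arm, the standard error would not cover the shift, and a change in attenders would be read as a change in glycaemia.

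The HbA1c result also decides whether the acceptability and utility co-primary is tested at all, so its interpretation matters beyond the one outcome.

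**Working it through.** **Step 1: the plan's own power.** Inputs from Sample size (14): difference 0.5, SD 2.3, intracluster correlation (ICC) 0.070, coefficient of variation (CV) of cluster size 0.730, 35 sites per arm, 3500 patients in total, significance level 0.05. Mean cluster size m = 3500 / 70 = 50.

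- Design effect, equal clusters: 1 + (50 − 1) × 0.070 = 4.43.
- Correction for unequal clusters: L = m × ICC / (m × ICC + 1 − ICC) = 3.5 / 4.43 = 0.790. Design effect = 4.43 / (1 − 0.730² × 0.790 × 0.210) = 4.86.
- Effective patients per arm: 35 × 50 / 4.86 = 360. SE = 2.3 × √(2 / 360) = 0.171.
- Power at 0.5: 83.1% (normal) or 82.0% (t, 68 df).

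The stated figure of at least 80% reproduces with this correction. A more conservative one, 1 + ((CV² + 1) × m − 1) × ICC = 6.30, gives 72.7% (normal) or 71.5% (t). That depends on the choice of formula and is not part of this point.

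**Step 2: who counts at follow-up.** Intervention resources open about three months before the report (Delivery). The report goes out in December 2021 (Feedback report). The audit window is May to July 2022, five to seven months later. Eligibility requires neither an earlier visit nor an HbA1c dated after any of these events. A person first seen in June 2022 counts the same as one under care throughout.

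**Step 3: what a case-mix difference would do.** If the arms differ by s in the share of a patient group whose mean HbA1c differs by g, the unadjusted contrast shifts by s × g. The documents give neither s nor g, so both are assumptions:

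| s | g = 0.5 | g = 1.0 | g = 1.5 |
|---|---|---|---|
| 5 points | 0.025 (5% of 0.5) | 0.05 (10%) | 0.075 (15%) |
| 10 points | 0.05 (10%) | 0.10 (20%) | 0.15 (30%) |
| 20 points | 0.10 (20%) | 0.20 (40%) | 0.30 (60%) |

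The shift can go in either direction.

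**Step 4: dilution, as a conditional calculation only.** If the 0.5 were an effect in exposed patients, and a share f of attenders could not yet have been reached, the expected contrast would be 0.5 × (1 − f). For f = 10%, 20% and 30% that is 0.45, 0.40 and 0.35, with power 74.7%, 64.6% and 53.3% (normal, design effect 4.86). The protocol states neither f nor the premise.

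**Step 5: can the model be adjusted?** The sample size counts 3500 patients, and the analysis section describes patients clustered in centres. Such a model needs patient-level records. Diabetes type and age must be on those records, because they decide who is extracted. The statement that investigators extract means and hold no individual data sits under secondary outcomes, but baseline HbA1c is likewise described as a centre mean. If only centre means were released, the stated model could not be fitted as written.

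**The case against.** The best defence is that this is a standard pragmatic design for a centre-level intervention. The outcome is described as HbA1c in people attending the centres, and its clock runs from report delivery. The protocol does not promise change in individuals exposed for six months. Consecutive sampling leaves unblinded centres little discretion, clinical measures are collected independently of the trial, and the audit data are checked. All of this stands.

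A reader might infer that the trial is underpowered because unexposed attenders dilute the effect. The documents do not support this. The sample size section does not say that 0.5 excludes patients not yet reached. If it is the average over attenders, nothing is lost. Unexposed patients also create no difference between arms by themselves.

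A reader might also infer that the intervention will change case mix, so that recall of poorly controlled patients makes effective QI look harmful. That is possible but not shown. The package is a webinar, change-champion stories and peer forums, and no section mentions recalling or discharging patients. Adjustment for age and type would not remove a shift in severity within those groups in any case.

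Finally, covariates are often left to an analysis plan, and the article never says that the centre intercept is the only term. Centre types are combined for analysis as well as stratification, so centre type has some role. This limits the point to an improvement of the stated model. It does not settle the tension between a patient-level model and the statement about data access, which is in the protocol itself.

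**Conclusion.** The concern holds as a modest, low-cost improvement. The HbA1c co-primary compares cross-sections of consecutive attenders identified after randomisation at unblinded centres, and the stated model names no patient-level adjustment. Any difference between arms in who attends enters the contrast. How large that is cannot be derived from the documents; the case-mix and dilution figures above are illustrations that rest on assumed shares and gaps. Neither bias nor a shortfall in power is shown. The repeated cross-section is a legitimate choice, provided the result is read as describing attenders.

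**What to change.** 1. In Statistical methods (20a), pre-specify diabetes type and age as patient-level covariates in the HbA1c mixed model, alongside arm and the centre intercept. The intervention cannot change either characteristic in a given patient, so adjusting for them does not remove a treatment effect.
2. Run that model on the patient-level audit records that it already requires, and reconcile this with the statement that investigators have no individual patient data by saying who holds the coded records and who fits the model.
3. Tabulate attender numbers, diabetes type and age by arm for 2021 and 2022. The 2021 audit window closed before the intervention resources opened, so it is the reference for any later shift.
4. State that the primary result is mean HbA1c of attenders at the 2022 audit.
5. Optional: if the audit form records visit type and HbA1c date (the form is not shown), add a supportive analysis of patients seen before the audit whose test postdates the start of the randomised package. That start is about three months before the report. The report date is not the right cut-off, because both arms receive the report. Note that this analysis conditions on attendance after randomisation.

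Cost: two covariates, one table, one sentence and possibly one supportive analysis, with no new data collection if the patient-level records can be used as in item 2. The adjustment removes only the part of a case-mix shift that type and age capture.
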